#### **D) Power/Sample Size Estimate:**

Expected Recruitment: At the time of this application we are collaborating with multiple ICCER-affiliated LTC organizations that wish to participate in this initiative. Most of these organizations have multiple facilities, many of which have multiple buildings or wings. Using Canadian Primary Care Sentinel Surveillance (CPCSSN) EMR data (accessed for the purpose of this application) we know that 53% of Canadians 80 yrs and older are listed as currently taking daily BP lowering medication. In our experience most of these medications are maintained upon nursing home admission. This suggests, given the 18-month median lifespan of newly admitted patients (and 9 month median lifespan of those already resident at the time of the study), that we should easily obtain 1200 residents total over the roughly 2-3-year duration of the trial.

Power: Utilizing well described methods for sample size determination, inflating the number of events to account for noncompliance, conservatively setting the median lifespan at 3 years to account for the inclusion of supportive living residents who, on average, live longer than the expected 18 months in long-term care facilities and assuming 33% of patients will be censored prior to any events, we find that 1232 patients would have 80% power (at a p of 0.05) to detect a difference between groups in the primary outcome of 27.6%. Although smaller differences would still be clinically meaningful, this difference is less than the 55% relative reduction in total mortality claimed in the MAPEC trial that we are trying to reproduce, and it is a very conservative minimum estimate for the actual power that the study will have. Additional power, while not directly calculable, will come in 2 ways: 1) These calculations assume no meaningful covariates and we have several covariates that are likely to be predictive of each outcome – in particular the resident's

level of care designation, and 2) we will continue to seek new facilities to partner with over the course of the trial – which should increase the number of residents available.

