Overall: We expect to randomize a minimum of 1200 residents and observe over a roughly 2-3 year period until 301 primary outcomes have occurred (with those outcomes being reported to us quarterly by the Alberta SPOR Data Platform). At a minimum this will provide sufficient power (80% power to detect a 27.6% difference) to validate or refute the MAPEC trials claim of a 55% reduction in mortality, and will likely provide substantial additional fidelity to detect smaller differences that are not currently calculable (as a result of meaningful covariates, continuous outcomes, and the expectation of additional facilities joining the project in coming months).

**E) Confirmation of data accuracy:** Prior to randomization the data steward will produce a list of all residents they believe to currently reside at each of the participating facilities. They will simultaneously request a list of all admitted residents from each participating facility and will compare these two lists to ensure there are no errors in identifying residents.

**F) Recruitment / Patient Flow:** (Flow Diagram - appendix pg. 6)

1. Informing Patients / Families / Primary Care Providers: Prior to facilities being randomized, we will send letters to all next of kin, and all attending primary care providers, notifying them that this study is taking place and that blood pressure medications might have their timing switched to bedtime. If family or physicians object, we will ask them to e-mail or call a toll free number to let us know the resident's name and the facility they reside in and we will exclude them from the timing change. A number will also be provided to speak with a BedMed physician if families or physicians have questions about the study.
2. Randomization: A minimum of one month after the last notification letter is mailed, eligible residents who have not opted out of participation will be randomized using random blocks of 2 or 4 with no stratification.

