# BedMed-Frail Statistical Analysis Plan

## **Adaptive Randomization (conversion to modified intention-to-treat)**

Participating facilities are volunteering to support our trial with no financial compensation, and “fitting it in” with other work. For several facilities, COVID-19, other infectious outbreaks, and implementation of other facility initiatives has led to long delays before the facility pharmacist was able to act on their allocation list. For a few facilities this delayed implementation by several months. Given 1) we are placing an equal emphasis on detecting harm, 2) long implementation delays make both groups look more similar and reduce the ability to detect harm, and 3) no action of any kind was taken related to the facility’s allocation list in this interval, we have adapted the trial to consider the date of each facility’s initial randomization to be the date the allocation list was actually acted upon, and not the date it was generated. This date was determined by the AHS data analyst, using electronic pharmacy dispensing data, to be the day before the first switch of an eligible patient’s BP medications from morning to bedtime. Individuals who, on the date of implementation, were no longer resident in the facility, hospitalized, or without once daily BP meds, were excluded from the trial.

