### *Cognitive / Behavioral*

5. “Deteriorated cognition relative to status 90 days prior”\*
6. “Behavioral symptoms that are present a minimum of 4 days per week and not easily altered in the last 7 days” (includes wandering, verbal abuse, physical abuse, socially inappropriate or disruptive behavior, and resisting care)\*

7. Receipt of antipsychotic medication or physical restraints (chair, trunk, or limb restraints, does not include bedrails) in the last 7 days\*
8. Receipt of anti-anxiety medication on  $\geq 3$  of the last 7 days\*
9. Receipt of a bedtime sleeping pill on  $\geq 3$  of the last 7 days\*
10. “Indicators of depression or anxiety almost daily” in the last 30 days (applies to 16 discrete mood and anxiety related observations of the resident, any one of which being listed as present 6 or more days per week would qualify)\*

\* Safety outcomes 2 – 10 will only be examined in LTC residents (and not Level 4 or 4D residents), as these measures are not as regularly collected on those who reside in facilities with a lower level of care. Each are binary outcomes as recorded by usual care nurses in the Quarterly RAI-MDS report in the 3- to 6-month window post-randomization (on average these assessments should take place roughly 135 days post-randomization, and the assessment closest to 135 days is chosen when more than one is available)

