| Secondary Safety (non-cognitive)                                             |                          |                                                                                                                                                                                                                                                                                                                                |
| Non-vertebral fracture                                                              | Cox Proportional Hazards | Facility/Level of Care specific non-vertebral fracture rate (prior 3 years), prior non-vertebral fracture, Gender, Age < 70, New admission*, Old admission †                                                                                                                                                        |
| Fall in the last 30 days                                                            | Poisson Regression       | Facility/Level of Care specific prior % fallers ‡ , Facility/Level of Care specific non-vertebral fracture rate (prior 3 years), New admission*, Old admission † , Gender                                                                                                                                |
| Urinary incontinence                                                                | Poisson Regression       | Facility/Level of Care specific prior % incontinent ‡ , New admission*, Old admission † , Age < 70, stroke, gender, diabetes                                                                                                                                                                             |
| Full thickness skin ulceration (stage 3 or 4)                                       | Poisson Regression       | Facility/Level of Care specific prior % ulcerated, ‡ New admission*, Old admission † , Stroke, Number of BP medications, Age < 70, gender                                                                                                                                                                |

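### The SAP assigns Poisson regression to nine binary safety outcomes without naming a robust variance; under the model-based default, standard errors are too large for common outcomes

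*Combined protocol and SAP*

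**What the plan says.** The SAP's outcome section lists ten secondary safety outcomes. Its footnote covers nine of them: "Safety outcomes 2 – 10 will only be examined in LTC residents". It then fixes their type and source: "Each are binary outcomes as recorded by usual care nurses in the Quarterly RAI-MDS report". One report per resident is used, the one closest to day 135 after randomisation.

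Table 2 (SAP, Selecting regression covariates) gives the method for each of the nine as "Poisson Regression":

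- non-cognitive: fall, urinary incontinence, skin ulceration;
- cognitive-behavioural: deteriorated cognition, behavioural symptoms, antipsychotic or restraint use, anti-anxiety drug, sleeping pill, indicators of depression or anxiety.

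The tenth, non-vertebral fracture, is analysed by Cox regression and is outside this point. Neither the protocol nor the SAP mentions a robust or sandwich variance, modified Poisson, log-binomial regression or clustered errors.

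On the weight given to harm, the SAP's section on adaptive randomization says: "we are placing an equal emphasis on detecting harm".

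**The concern.** A Poisson model sets the variance equal to the mean. For a yes/no outcome with risk p, that means variance p where the true variance is p(1 − p). The risk ratio is still estimated consistently, but the model-based standard error is too large. Confidence intervals are then too wide and the test rejects less often than its nominal level.

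For an efficacy claim this error is conservative. For a harm question it works the other way, because a real increase in falls, incontinence or sedative use is more likely to be reported as no clear difference. That sits badly with a trial that gives harm equal emphasis and enrols residents under a waiver of consent.

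**Working it through.** **Inputs from the documents.** Nine binary outcomes, one report per resident, method as in Table 2. Allocation is by resident, in "random blocks of 2 or 4 with no stratification". The significance level is 0.05.

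**Assumed inputs.** The documents give neither prevalences nor the number of long-term care residents. I use prevalences from 2% to 70% and 200, 400 or 600 residents per arm.

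**The plan's own power figure.** The protocol states that "1232 patients would have 80% power (at a p of 0.05) to detect a difference between groups" of 27.6% in the primary outcome, with 301 events. Reading this as a hazard ratio of 0.724, two-sided, Schoenfeld's formula gives 4 × (1.960 + 0.842)² / (ln 0.724)² = 301 events. The figure reproduces. It concerns the primary outcome only; no power is stated for the nine safety outcomes.

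**Variance of the log risk ratio, n per arm, risks p0 and p1.**

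- Model-based Poisson: 1/(n·p0) + 1/(n·p1)
- Correct (binomial, which the sandwich estimates): (1 − p0)/(n·p0) + (1 − p1)/(n·p1)
- With p0 = p1 = p, the ratio of standard errors is 1/√(1 − p)
- Actual two-sided type I error: 2 × [1 − Φ(1.96/√(1 − p))]
- Power with the model-based error: Φ[(ln RR − 1.96·SE_model)/SE_correct]

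**One case in full: n = 400, p0 = 0.50, RR = 1.20, so p1 = 0.60.**

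- Correct variance: 0.5/200 + 0.4/240 = 0.00417, SE 0.0645
- Model-based variance: 1/200 + 1/240 = 0.00917, SE 0.0957
- ln 1.20 = 0.1823
- Power, correct SE: Φ(0.1823/0.0645 − 1.96) ≈ 81%
- Power, model-based SE: Φ[(0.1823 − 1.96 × 0.0957)/0.0645] ≈ 47%

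Solving for the risk ratio that gives exactly 80% (1.20 after rounding) puts the model-based figure at 46%.

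**Over the assumed range, 400 per arm:**

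| Prevalence | SE ratio | Type I error at nominal 5% | RR with 80% power, robust | Power, model-based |
|---|---|---|---|---|
| 2% | 1.01 | 4.8% | 3.07 | 79% |
| 10% | 1.05 | 3.9% | 1.69 | 76% |
| 20% | 1.12 | 2.8% | 1.43 | 71% |
| 30% | 1.20 | 1.9% | 1.32 | 65% |
| 50% | 1.41 | 0.6% | 1.20 | 46% |
| 70% | 1.83 | 0.03% | 1.12 | 15% |

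With 200 or 600 per arm the model-based power is 44% or 47% at 50% prevalence, and 12% or 16% at 70%.

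**Check by simulation** (400 per arm, 15 facilities assumed, 1,000 runs per setting, no treatment effect, no covariates):

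| Prevalence | Empirical SD | Mean SE, model-based | Mean SE, robust | Rejections, model-based | Rejections, robust |
|---|---|---|---|---|---|
| 10% | 0.2147 | 0.2259 | 0.2145 | 3.8% | 4.8% |
| 30% | 0.1072 | 0.1295 | 0.1085 | 2.2% | 4.3% |
| 50% | 0.0715 | 0.1002 | 0.0710 | 0.6% | 5.5% |
| 70% | 0.0483 | 0.0846 | 0.0464 | 0.3% | 5.8% |

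At 50% prevalence and RR 1.20, simulated power was 48% model-based and 82% robust. At 2% prevalence the mean model-based standard error was unusable (15.2, against an empirical SD of 0.89), as happens when an arm has no events in some runs. Rejection rates there were 2.7% and 2.8%, so the choice of variance hardly mattered.

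**Variation between facilities.** With baseline risk varying by facility (SD 0.7 on the logit scale, 50% prevalence), the mean model-based standard error was 0.1004 against an empirical SD of 0.0687. The direction did not change.

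**Covariates.** The formulas are for the unadjusted comparison, whereas Table 2 adds covariates. If the mean model is right, each resident's true variance μ(1 − μ) is still below the assumed μ, so the direction holds. The size with covariates was not computed.

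**The case against.** The strongest reply is that the SAP has left something out and has not made a wrong choice. Table 2's method column carries only model names and gives no variance estimator for any model, the primary Cox model included. The authors plainly knew the outcomes were binary: the footnote says so, and the covariate rule has its own limit for dichotomous outcomes. Analysts who fit Poisson models to binary data to obtain risk ratios commonly use a sandwich variance, so the label fits sound practice too. This stands. A reader might infer that the SAP prescribes the model-based variance; the documents do not say that. What remains is that a plain Poisson fit implies that variance, and nothing in the SAP requires another. A plan that fixes the order of covariates should not leave this choice open until results are visible.

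Second, the large losses come only from the assumed prevalences of 50% and 70%. This also stands as a limit on size. A reader might infer that all nine tests fall far below nominal level, but at 10% prevalence type I error is 3.9% and power 76% against 80%.

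Third, these are secondary outcomes without a stated power target, and the error cannot create a false harm signal. That bears on severity; it does not remove the need to specify the variance.

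A reader might also link this to the October 2024 entry in the amendment log, which asks facilities to keep their allocations partly because no harm had been shown. The documents do not say which variance lay behind that statement, so it cannot be called a product of inflated intervals.

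**Conclusion.** The point holds as an unspecified variance estimator whose default is wrong for binary data. If the default is used, standard errors are too large by about 1/√(1 − p). The effect is negligible at a few percent prevalence, moderate near 30% and serious from about 50% upward.

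Which outcomes fall where is not known from the documents. Skin ulceration may be rare, although the outcome list counts stages 2 to 4 and the Table 2 row only stages 3 or 4. Urinary incontinence, counted from two episodes a week, may be common.

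The direction rests on algebra. The size rests on assumed prevalences, an assumed 200 to 600 residents per arm and an unadjusted comparison. Risk-ratio estimates are untouched, as are the Cox analyses of the primary outcome, mortality, hospitalisation and fracture. The severity is should-fix: it affects intervals, p-values and power for secondary safety outcomes, in a trial that says harm matters equally.

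**What to change.** In all nine Table 2 rows, replace the method with *modified Poisson regression (log link, robust sandwich variance) for the risk ratio*. The Poisson model itself need not be replaced.

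State whether the variance is clustered by facility. An unclustered sandwich is a reasonable default because residents are randomised individually. If it is clustered, name a small-sample correction: with 15 assumed facilities, the uncorrected cluster sandwich rejected in about 6% to 9% of null simulations at prevalences of 10% to 70%. One caution on the default is that when the treatment effect itself varied between facilities (SD 0.1 on the log scale, 50% prevalence), the unclustered sandwich rejected in 7.1% of runs and the clustered one in 7.2%.

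Where these outcomes have already been analysed, report which variance was used and rerun any model-based results. The cost is one phrase in the SAP and one option in the code, with no change to data collection or trial conduct.

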## **Statistical Analysis**

### **Intension-to-treat assumptions**

*Loss to follow-up:* If participants change continuing care facilities within Alberta, we will no longer be able to control their medication timing, which is likely to default to morning use upon entering a new facility. As such, we will censor residents who change facilities on the first day of residence in the new continuing care facility. However, we will not censor patients transferred to “inpatient LTC” at a local hospital, as that is likely to represent an escalation in care due to acute illness, or diminished capacity. If such individuals improve, they may return to the original continuing care facility and we can continue to follow them. If not, the transfer to “inpatient LTC” likely signals a

deterioration of health that may precede adverse health outcomes that would be important to capture. If residents change their level of care, but remain in the same facility (i.e. move to a different floor, or wing, which has a different level of care), we will continue to follow them, as their medication timing is unlikely to change.

*Withdrawal:* Residents who do not want to participate in BedMed-Frail are generally “opted out” (i.e. excluded) prior to randomization. Should we be approached, by a resident, their family, or their providers, to opt-out a resident after randomization, that is likely to be prompted by an attempted timing change, and hence a more likely occurrence for those allocated to bedtime. To avoid the introduction of attrition bias, all post-randomization opt-outs will be included and analyzed per their allocation unless we are explicitly asked not to follow their electronic health data.

*Missing MDS data:* For each analysis, we will use the post-randomization MDS nursing report closest to day 135 (tie going to the later date). If there are no such post-randomization reports we will use the report immediately preceding randomization. If no reports of any kind are available (which should not occur as a baseline MDS report is a routine part of every admission), we will exclude the participant from the analysis.

*Nonadherence:* Nonadherence to allocation will not exclude participants from any of our planned analyses. However, as outlined in Sensitivity Analysis below, we will conduct a per-protocol analysis to determine whether results differ when adherence to allocation is highest.

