| “Deteriorated cognition relative to status 90 days prior”                                                                                                                                                                                                                                                                                                                                    | Poisson Regression         | Facility/Level of Care specific prior % deteriorated ‡ , Age <70, New admission*, Old admission † , gender                                                                                                                                                                           |
| “Behavioral symptoms that are present a minimum of 4 days per week and not easily altered” (Includes wandering, verbal abuse, physical abuse, socially inappropriate or disruptive behavior, and resisting care)                                                                                                                                                                             | Poisson Regression         | Facility/Level of Care specific prior % behavior problems ‡ , New admission*, Old admission † , Gender, Age < 70, Days hospitalized in prior 6 months, Number of ED visits in prior 6 months, Total number of non-BP medications, Total number of BP medications, Charlson score     |
| Receipt of antipsychotic medication or physical restraints in the last 7 days                                                                                                                                                                                                                                                                                                                | Poisson Regression         | Same as above                                                                                                                                                                                                                                                                                              |

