| Cost                                                                                                                                                                                                                                                                                                                                                                                  |                            |                                                                                                                                                                                                                                                                                                            |
| Acute care costs

Total cost of care                                                                                                                                                                                                                                                                                                                                                   | Multiple Linear Regression | Facility, Level of Care § , Age <70, New admission*, Old admission † , Gender, Days hospitalized in prior 6 months, Number of ED visits in prior 6 months, Charlson score, Total number of non-BP medications, Total number of BP medications, CHF, COPD, diabetes, CAD, stroke, CKD |
| * Resident in current facility less than 60-days at time of randomization
† Resident in current facility more than 3-years at time of randomization
‡ % of all RAI-MDS reports from this facility over the last 3-years indicating this outcome
§ In order of increasing care, this includes: Levels 3, 4, 4D, and 5 (as described in the manuscript under Setting and Recruitment) |                            |                                                                                                                                                                                                                                                                                                            |

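### The nine RAI-MDS safety models adjust for a facility's historical percentage but not for the resident's own baseline value of the same item, which costs precision without causing bias

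*Combined protocol and SAP*

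**What the plan says.** Secondary safety outcomes 2 to 10 are binary items from the quarterly RAI-MDS report, examined in LTC residents only. SAP Table 2 assigns each one Poisson regression and a covariate list led by a facility figure:

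- falls: "Facility/Level of Care specific prior % fallers"
- urinary incontinence: "Facility/Level of Care specific prior % incontinent"
- skin ulceration: "Facility/Level of Care specific prior % ulcerated"
- deteriorated cognition: "Facility/Level of Care specific prior % deteriorated"
- behavioural symptoms: "Facility/Level of Care specific prior % behavior problems"

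The four remaining rows (antipsychotic or restraint, anti-anxiety drug, sleeping pill, depression or anxiety) refer back to the behaviour list. A footnote defines the figure as the percentage "of all RAI-MDS reports from this facility over the last 3-years indicating this outcome".

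The rest of each list is a mix of admission timing, age under 70, gender, comorbidities, medication counts, prior hospital or ED use, Charlson score and the facility fracture rate. No list names the resident's own earlier value of the outcome item. The lists are predefined, taken in order and capped at one covariate per 10 outcomes (SAP, Selecting regression covariates), so nothing outside them enters.

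The SAP's paragraph on missing MDS data says that "a baseline MDS report is a routine part of every admission". Its only stated role for that record in the outcome analysis is as a stand-in: "If there are no such post-randomization reports we will use the report immediately preceding randomization". The non-vertebral fracture model, which does not use MDS data, lists both the facility rate and the resident's own prior fracture.

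**The concern.** A facility percentage takes one value for all LTC residents of a facility, so it cannot separate two residents of the same home. Several of the outcomes are states that tend to persist: a resident who is incontinent, or takes a sleeping pill most nights, is likely to be so again some four months later. The resident's own earlier value of the item is then a natural covariate, and the SAP expects it to be on file.

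Two things are at stake. One is the width of the safety intervals, in a SAP that says it weights detection of harm equally (Adaptive Randomization). The other is chance imbalance: randomisation is in blocks of 2 or 4 without stratification (protocol, Recruitment / Patient Flow), and a facility average cannot correct a chance difference in residents' own baseline status.

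**Working it through.** **1. The plan's own figure.** The documents state no prevalence, correlation or power for any MDS outcome. The only design figure is 301 primary-outcome events for 80% power at two-sided 0.05 and a 27.6% reduction. Schoenfeld's formula gives 4 × (1.960 + 0.842)² / (ln 0.724)² = 4 × 7.849 / 0.1043 = 301. It reproduces, and the present point does not affect it.

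**2. Gain from own baseline status.** Let φ be the correlation between the baseline item and the follow-up item. In large samples, adjusting for the baseline item multiplies the variance of the log rate ratio by 1 − φ², which equals 1/(1 − φ²) times the sample size. All values of φ are assumptions.

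| φ | 1 − φ² | Variance reduction, simulated | Sample-size equivalent |
|---|---|---|---|
| 0.1 | 0.99 | about 1% | 1.01 |
| 0.2 | 0.96 | about 4% | 1.04 |
| 0.4 | 0.84 | about 16% | 1.19 |
| 0.5 | 0.75 | about 25% | 1.33 |
| 0.6 | 0.64 | about 36% | 1.56 |
| 0.7 | 0.51 | about 48% | 1.92 (1/0.52, simulated) |

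**3. Gain beyond the facility percentage.** A second simulation kept the facility percentage in the model. It assumed 600 LTC residents, 15 facilities, prevalence 15% or 60%, and facility intraclass correlation (ICC) 0.02 or 0.10, with 400 runs per setting. The facility percentage alone removed about 2% of the variance at ICC 0.02 and about 8–9% at ICC 0.10. Adding own baseline removed a further 3–4% at φ = 0.2, 13–16% at φ = 0.4 and 33–36% at φ = 0.6 (robust standard errors).

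**4. Does the gain reach the reported intervals?** Table 2 says Poisson regression and names no robust variance. For a binary outcome, the model-based Poisson variance of the log rate ratio is close to 1/E₁ + 1/E₀, where E is the number of events per arm, whatever baseline covariates are added. With 300 per arm and 60% prevalence, E = 180 and the standard error is √(2/180) = 0.105. The actual unadjusted value is √(2 × 0.4/180) = 0.067. In the simulation at prevalence 60%, φ = 0.6 and ICC 0.10, adding own baseline took the robust standard error from 0.0643 to 0.0515 (ratio 0.801, variance reduction 36%). The model-based one stayed at 0.1062. The estimate becomes less variable, but without robust variance the printed interval does not show it.

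**5. Chance imbalance.** Assume 300 per arm, 30% baseline prevalence and φ = 0.5. The standard error of the baseline difference is √(2 × 0.3 × 0.7/300) = 0.0374, so one draw in 20 differs by at least 1.96 × 0.0374 = 7.3 points. About half, 3.7 points, carries to follow-up: roughly 31.8% against 28.2%, a rate ratio of 1.13 with no true effect. Adjusting for own baseline largely removes this.

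**6. Interaction with the missing-data rule.** A resident with no post-randomisation report has the last pre-randomisation value entered as the outcome. If that same value becomes a covariate, outcome equals covariate for those residents and the model looks better predicted than it is.

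**The case against.** The plan contains no error here. Allocation is at resident level, so the comparison is valid with any set of baseline covariates. The lists are fixed, ordered and free of stepwise selection. Only secondary safety outcomes are affected. All of this stands.

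A reader might go further and infer that the SAP discards the strongest available predictor. The documents do not support that, because they report no within-resident correlation. At φ = 0.2 and facility ICC 0.10, own baseline adds 3–4% while the facility percentage yields 8–9%. Falls in the last 30 days are episodic, and deteriorated cognition is already a change from 90 days before, so low correlations are plausible for both. A reader might also infer that the safety results are biased; individual randomisation rules that out.

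It is also fair to say that a wording change to the covariate list alone would not narrow the reported intervals (step 4) and would clash with the fallback rule (step 6). Finally, the SAP is described as the only version, made before the interim analysis, and the amendment log's October 2024 entry shows that outcome results had been seen by then.

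What remains is that the SAP pairs a facility rate with the resident's own history for fractures but not for any MDS outcome, and gives no reason. It already treats the earlier report as an acceptable proxy for follow-up status. The protocol's power section also counts on predictive covariates for extra power.

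**Conclusion.** The point holds as an avoidable loss of precision and an uncorrected exposure to chance imbalance in all nine RAI-MDS safety models. Its size runs from negligible (about 1% of the variance at φ = 0.1) to substantial (about 48% at φ = 0.7), or about 1.0 to 1.9 times the sample size. It rests on assumed correlations, and it reaches the printed intervals only if robust variance is used. The larger gains are to be expected for continence, antipsychotic or restraint use, anti-anxiety and sleeping-pill receipt, and behavioural symptoms; the smallest for falls and deteriorated cognition. The primary outcome and its 301 events are untouched.

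**What to change.** Three changes belong together.

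1. For the persistent items at least, put the resident's own value on the last pre-randomisation MDS report first in the Table 2 list, ahead of the facility percentage. First place matters because the one-per-10 rule works down the list.
2. Specify Poisson regression with robust (sandwich) variance for the binary MDS outcomes.
3. Stop using the pre-randomisation report as the outcome in the main analysis. One option is to analyse residents who have a follow-up report and keep the fallback as a sensitivity analysis. That set depends on survival and continued stay until the assessment, which the SAP should acknowledge.

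While editing, state whether the four rows that refer back to the behaviour list use the facility percentage for behaviour problems or for their own outcome.

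The cost is one covariate slot, or two if a missing-report indicator is needed, so 10 or 20 outcome events under the SAP's rule. For a rare outcome, as stage 3–4 ulceration may be, that could displace the facility percentage or another covariate. The outcome list gives stages 2 to 4 where Table 2 gives 3 or 4; the event count depends on which applies, so the two must be reconciled. No new data collection is needed. If results are already known, keep the prespecified models and report these as a labelled supplementary analysis.
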